## Abstract

**Background:**

Augmented mindfulness-based cognitive therapy (MBCT) with treatment as usual (mainly pharmacotherapy) is reported to be effective after treatment for anxiety disorders. However, whether its effectiveness persists in the long term is unclear.

**Objective:**

This study aims to examine the feasibility, acceptability, and effectiveness of a follow-up program by conducting a feasibility randomized controlled trial (RCT) that compares augmented MBCT with follow-up sessions and that without follow-up sessions in preparation for a definitive RCT.

**Methods:**

The study involves an 8-week MBCT with a 10-month follow-up. Patients aged 20 to 65 years who meet the Diagnostic and Statistical Manual of Mental Disorders, 4th edition (DSM-IV) criteria for panic disorder, agoraphobia, or social anxiety disorder, which is not remitted with usual treatment for at least 4 weeks, will be included in the study and randomly allocated to receive augmented MBCT with follow-up sessions or augmented MBCT without follow-up sessions. For this feasibility RCT, the primary outcomes are (1) study inclusion rate, (2) dropout rate, (3) attendance rate, and (4) mean and standard deviation of several clinical measures at 8 weeks and 5, 8, and 12 months.

**Results:**

We started recruiting participants in January 2020, and 43 participants have been enrolled up to January 2021. The study is ongoing, and data collection will be completed by May 2022.

**Conclusions:**

This study is novel in terms of its design, which compares augmented MBCT with and without follow-up sessions. The limitations of the trial are as follows: (1) mixed participants in terms of the delivery mode of the intervention, and (2) lack of a pharmacotherapy-alone arm. Owing to its novelty and significance, this study will provide fruitful knowledge for future definitive RCTs.

**Trial Registration:**

UMIN Clinical Trials Registry UMIN000038626; https://tinyurl.com/2p9dtxzh

**International Registered Report Identifier (IRRID):**

DERR1-10.2196/33776

## Introduction

### Background

Anxiety disorders are the most prevalent mental disorders worldwide [1]. The global 12-month prevalence rate is estimated to be 7.3% [2,3], although prevalence varies across regions (eg, from 3.3% to 18.1% [4-6]). The early age of onset [7] and high probability of relapse [8] prolong the course of the disease, negatively affecting patients socially and chronically [9]. The cumulative remission rates are as low as 35% for social anxiety disorders, 42% for panic disorders with agoraphobia, and 50% for generalized anxiety disorders over a 10-year period [10]. Such features of the disorder place a considerable burden on society. In 2015, anxiety disorders were the sixth leading contributor to nonfatal health loss globally, generating a global total of 24.6 million years lost due to disability [11]. The impact becomes more obvious when the burden is converted into a monetary measure. The societal costs of anxiety disorders were 42.3 billion USD in the United States (1990) [12], 8.9 billion GBP (11.9 billion USD) in the United Kingdom (2007) [13], and 2.4 trillion JPY (27 billion USD) in Japan (2008) [14].

Major clinical guidelines suggest pharmacotherapy and cognitive behavioral therapy (CBT) as the recommended treatments for anxiety disorders [15-17]. However, because of an overwhelming shortage of CBT therapists, a limited number of patients (4.5% in the United States) are able to access CBT [18]. Consequently, pharmacotherapy is currently the dominant treatment strategy. Although the effectiveness of pharmacotherapy for anxiety disorders has been confirmed, remission rates remain between 25% and 35% [19]. Therefore, developing a subsequent treatment for pharmacotherapy-refractory patients, which is effectual and cost-effective in the long term, is important.

Mindfulness-based cognitive therapy (MBCT) [20], which integrates mindfulness-based stress reduction (MBSR) programs with the essence of CBT [21], is a candidate option. MBCT cultivates mindfulness and nonjudgmental present-moment awareness, which allows people to become aware of their bodily sensations, feelings, and thoughts. MBCT is normally offered in a group format and could be more efficient than individual CBT.

### What We Already Know

MBCT has a significant favorable effect on anxiety disorders [22-28]. Even in a setting where the majority of patients manifest pharmacotherapy resistance, MBCT augmented with pharmacotherapy appears to be more effective than pharmacotherapy alone at posttreatment [29]. However, its long-term effectiveness is unclear. For treatment-resistant depression, Eisendrath et al [30] showed that the effects of augmented MBCT on the reduction of Hamilton Depression Rating Scale scores at posttreatment disappeared 1 year later. One possible explanation is that termination of the treatment discourages patients from continuing to practice mindfulness meditation posttreatment.

### Rationale for the Study

As Segal et al indicated [31], although the practice time does not directly affect the clinical outcome, it could affect the outcome mediated by the “decentering” skill improved by the meditation practice. Given that the practice time diminishes as the intervention terminates [32], adding follow-up sessions posttreatment would encourage patients to practice meditation continuously, possibly leading to a better outcome through the improvement of the core skill of decentering. Therefore, in anticipation of future definitive randomized controlled trials (RCTs), we decided to conduct a feasibility RCT to compare augmented MBCT (ie, MBCT plus pharmacotherapy) with follow-up sessions and augmented MBCT without follow-up in order to (1) assess the feasibility, safety, and effectiveness of augmented MBCT with follow-up sessions and (2) compare clinical outcomes between the 2 arms.

### Aim

This study aims to examine the feasibility, acceptability, and effectiveness of a follow-up program in an augmented MBCT scheme by conducting a feasibility RCT between augmented MBCT with and that without follow-up sessions.

## Methods

### Participants

The study is being conducted at Keio University Hospital in Tokyo, Japan. We will recruit participants from the Department of Neuropsychiatry. Patients are eligible for the study if they are between the ages of 20 and 65 years; meet the Diagnostic and Statistical Manual of Mental Disorders, 4th edition (DSM-IV) criteria for panic disorder, agoraphobia, or social anxiety disorder, which is not remitted with usual treatment (pharmacotherapy) for at least 4 weeks; and are capable of providing written consent. The exclusion criteria are substance abuse or dependence, antisocial personality disorder, severe suicidality, self-harm, organic brain damage, severe physical illness, and other appropriate factors deemed by the principal investigator. Patients who are unlikely to attend for 12 months (eg, expected to be moving) will be excluded.

### Baseline Assessment

Participants will be asked to fill a battery of questionnaires relevant to demographic and psychosocial data. Psychological scales include the State-Trait Anxiety Inventory (STAI), Panic and Agoraphobia Scale (PAS), Liebowitz Social Anxiety Scale (LSAS), Experiences Questionnaire (EQ), Short-Form 36-Item Health Survey (SF-36), Scale of Positive and Negative Experience (SPANE), Rosenberg Self-Esteem Scale (RSES), Five Facet Mindfulness Questionnaire (FFMQ), Connor Davidson Resilience Scale (CDRISC), Self-Compassion Scale (SCS), 16-item Quick Inventory of Depressive Symptomatology (QIDS), Generalized Anxiety Disorder Assessment-7 (GAD7), Perceived Stress Scale (PSS), World Health Organization Health and Work Performance Questionnaire (WHO-HPQ), Satisfaction With Life Scale (SWLS), Flourishing Scale (FS), Multidimensional Assessment of Interoceptive Awareness (MAIA), EuroQoL-5 Dimensions (EQ-5D), health care service use (including medication), Hamilton Anxiety Scale (HAM-A), and interoception. All assessments, except for the latter 2 (ie, HAM-A and interoception), are intended to be conducted in a self-report format.

### Randomization

Eligible participants will be randomly allocated to either the augmented MBCT with follow-up sessions group or MBCT without follow-up sessions group (1:1 ratio). A computer-generated random number stratified by diagnosis (ie, panic disorder/agoraphobia and social anxiety disorder) and baseline score for the STAI will be assigned to each participant. The Project Management Office at Keio Center of Clinical Research, which is an independent institution from the study group, will manage the randomization process. The flow of the recruitment of participants is shown in Figure 1.

**Figure 1 figure1:**
[figure not shown]
Flow of the study. MBCT: mindfulness-based cognitive therapy.

### Blinding

The randomization status will not be blinded to both participants and therapists because of the nature of the psychological intervention. The raters blind to the allocation status will perform assessments for interoception and HAM-A. Both participants and therapists will be strongly indicated not to report their treatment allocation at rater-administered assessments. The assessors are independent and not involved in the treatment administration.

### Interventions

#### MBCT With Follow-up Sessions Group

The patients in the intervention group will be offered an 8-week MBCT followed by a 10-month follow-up program. The MBCT consists of 8 weekly sessions in a group format. Each session lasts for 2 hours. In the program, participants practice mindfulness meditation as well as cognitive exercise. Minimum modifications have been made to the original version of MBCT [20] because the study targets patients with anxiety disorders rather than those with depression. Specifically, we have replaced psychoeducation of depression with that of anxiety. Table 1 describes the themes and contents of each session. The participants will be requested to practice mindfulness meditation for approximately 30 minutes daily and to record the duration of time they meditated and the meditation type.

**Table 1 table1:** Themes and content of the program.

Session	Theme	Content
1	Automatic pilot	Psychoeducation: What is mindfulness? Exercise: Mindfulness eating (“raisin exercise”)/body scan Homework: Mindfulness of a routine activity/body scan
2	Dealing with barriers	Psychoeducation: Association of mood and thoughts Exercise: Thoughts and feelings exercise/body scan/mindful breathing meditation Homework: Body scan/breathing meditation/pleasant events calendar
3	Mindfulness of the breath	Psychoeducation: Awareness of mind wandering and focusing on the breath Exercise: Breathing meditation/gentle yoga/mindful walking Homework: Breathing meditation/gentle yoga/mindful walking/unpleasant events calendar
4	Staying present	Psychoeducation: Staying present/about anxiety symptoms^a^ Exercise: Meditation of sounds and thoughts/breathing meditation Homework: Meditation of sounds and thoughts/breathing meditation/3-minute breathing space
5	Allowing/letting be	Psychoeducation: Exploring difficulty Exercise: Breathing meditation/meditation of sounds and thoughts/exploring difficulty Homework: Breathing meditation/meditation of sounds and thoughts/exploring difficulty/3-minute breathing space
6	Thoughts are not facts	Psychoeducation: Cognitive biases Exercise: Breathing meditation/meditation of sounds and thoughts/exploring difficulty Homework: Breathing meditation/meditation of sounds and thoughts/exploring difficulty/3-minute breathing space

#### MBCT Without Follow-Up Sessions Group

Participants in the control group will also be offered the 8-week MBCT. During the follow-up period, they will be encouraged to continue practicing by themselves. However, no additional intervention is intended to be provided after the 8-week MBCT.

#### Response During the COVID-19 Pandemic

MBCT and follow-up sessions were initially planned to be offered in person. However, to ensure participant safety during the COVID-19 pandemic, classes will be offered online.

### Outcomes

#### Primary Outcomes

In this feasibility RCT, the primary outcomes are the (1) study inclusion rate, (2) dropout rate, (3) attendance rate, and (4) mean and standard deviation of the below clinical measures at 8 weeks and 5, 8, and 12 months.

#### Clinical Outcomes

The primary clinical outcome is the mean and standard deviation of the STAI score in both groups at 8 weeks and 5, 8, and 12 months after the start of the intervention. The mean difference and standard deviation of the STAI score between the groups is also assessed.

The secondary clinical outcomes are PAS, LSAS, EQ, SF-36, SPANE, RSES, FFMQ, CDRISC, SCS, QIDS, GAD7, PSS, WHO-HPQ, SWLS, FS, MAIA, EQ-5D, HAM-A, and interoception scores (baseline, 8 weeks, and 12 months only for HAM-A and interoception); health service use; engagement in meditation practice; and satisfaction with and expectation of the classes.

#### Cost-effectiveness

Cost-effectiveness is assessed by the incremental cost-effectiveness ratio, which represents the incremental cost divided by the incremental effectiveness between the groups. Incremental effectiveness is evaluated using quality-adjusted life years calculated from the results of EQ-5D. The analyses are conducted from a health care system perspective.

### Instruments

#### STAI

The STAI is a commonly used measure of state and trait anxiety. It can be used in clinical settings to diagnose anxiety and distinguish it from depressive syndromes. It has 20 items for assessing trait anxiety and 20 for assessing state anxiety. Possible scores range from 20 to 80. Higher scores indicate higher anxiety [34].

#### PAS

The PAS is a measure of illness severity in patients with panic disorder (with or without agoraphobia). It has 13 items with a 5-point scale, which covers the following 5 subscales: panic attacks, agoraphobic avoidance, anticipatory anxiety, disability, and functional avoidance (health concerns). Higher scores indicate more severity [35].

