#### LSAS

This instrument is used to assess patients’ fear in a range of social interactions and performance situations. The scale consists of 24 items, which are categorized into the following 2 elements: performance anxiety (13 items) and social situations (11 items). Scores are between 0 and 144, with higher scores indicating higher social anxiety [36].

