### Schedule for Assessments

All participants will be requested to fill the self-report measures at 4 weeks (the intervention midpoint) and 8 weeks (postintervention), and at 3, 6, and 10 months postintervention, as well as complete the baseline assessments. HAM-A and interoception will be assessed at baseline (0 weeks), at the end of the MBCT (8 weeks), and at 10 months postintervention. We will allow for a range of ±2 weeks from the scheduled evaluation date for the evaluation during the intervention period and ±4 weeks from the scheduled evaluation date for the evaluation during the follow-up period. For those who are unable to come to the hospital to complete the self-rated scales, we will contact them and ask them to fill out and return the above evaluation items by mail or telephone. The assessment schedule is presented in Table 2.

**Table 2 table2:** Schedule of assessments

	Study period																			
	Screening period	Intervention period									Follow-up period									
Timepoint		1 wk	2 wk	3 wk	4 wk	5 wk	6 wk	7 wk	8 wk	1 mo		2 mo	3 mo	4 mo	5 mo	6 mo	7 mo	8 mo	9 mo	10 mo
Screening (SCID^a^, etc)	✓																			
Informed consent	✓																			
MBCT with f/u^b^		✓	✓	✓	✓	✓	✓	✓	✓	✓		✓	✓	✓	✓	✓	✓	✓	✓	✓
MBCT without f/u^c^		✓	✓	✓	✓	✓	✓	✓	✓											
STAI^d^	✓				✓				✓				✓			✓				✓
PAS^e^	✓				✓				✓				✓			✓				✓
LSAS^f^	✓				✓				✓				✓			✓				✓
EQ^g^	✓				✓				✓				✓			✓				✓
SF-36^h^	✓				✓				✓				✓			✓				✓
SPANE^i^	✓				✓				✓				✓			✓				✓
RSES^j^	✓				✓				✓				✓			✓				✓
FFMQ^k^	✓				✓				✓				✓			✓				✓
CDRISC^l^	✓				✓				✓				✓			✓				✓
SCS^m^	✓				✓				✓				✓			✓				✓
QIDS^n^	✓				✓				✓				✓			✓				✓
GAD7^o^	✓				✓				✓				✓			✓				✓
PSS^p^	✓				✓				✓				✓			✓				✓
WHO-HPQ^q^	✓				✓				✓				✓			✓				✓
SWLS^r^	✓				✓				✓				✓			✓				✓
FS^s^	✓				✓				✓				✓			✓				✓
MAIA^t^	✓				✓				✓				✓			✓				✓
EQ-5D^u^	✓				✓				✓				✓			✓				✓
HAM-A^v^	✓								✓											✓
Interoception	✓								✓											✓
Health service use	✓				✓				✓				✓			✓				✓
Homework engagement		✓	✓	✓	✓	✓	✓	✓	✓	✓		✓	✓	✓	✓	✓	✓	✓	✓	✓

^a^SCID: Structured Clinical Interview for Diagnostic and Statistical Manual of Mental Disorders, 4th edition disorders.

^b^MBCT with f/u: mindfulness-based cognitive therapy with follow-up sessions.

^c^MBCT without f/u: mindfulness-based cognitive therapy without follow-up sessions.

^d^STAI: State-Trait Anxiety Inventory.

^e^PAS: Panic and Agoraphobia Scale.

^f^LSAS: Liebowitz Social Anxiety Scale.

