### Statistical Analysis

Statistical analyses and reporting of this trial will be conducted with primary analyses based on the intention-to-treat approach. The full analysis set will include all randomized subjects administered at least one procedure of the investigational treatment. For baseline variables, we will generate summary statistics with proportions and frequencies for categorical variables, and means and standard deviations for continuous data. Statistical data relevant to feasibility will be presented descriptively. For primary and secondary clinical outcome analyses, we will analyze mean changes from baseline with a restricted maximum likelihood-based repeated measures approach. The mixed model for repeated measures analyses will include the fixed and categorical effects of treatment, visit, and the treatment×visit interaction. We will employ Kenward-Roger approximation to estimate the degrees of freedom of the denominator. We will not conduct any adjustment for multiple testing of secondary outcomes because of the exploratory nature of the study. Imputation will not be performed for missing values because mixed models can deal with missing data by maximum likelihood. All comparisons are planned, and all P values are two-sided. A 5% significance level will be set for all statistical analyses. All statistical analyses will be conducted using Stata version 16 (Stata Corp).

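### As written, PAS and LSAS are summarised and modelled only across all diagnoses, so their means, SDs and arm differences depend on the recruitment mix (minor)

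*Protocol article*

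**What the plan says.** All references are to the protocol article.

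- **Participants** admits patients who meet "criteria for panic disorder, agoraphobia, or social anxiety disorder". Comorbidity between these is not an exclusion.
- **PAS** (Instruments): "The PAS is a measure of illness severity in patients with panic disorder (with or without agoraphobia".
- **LSAS** (Instruments) is described as assessing "fear in a range of social interactions and performance situations". Higher scores mean more social anxiety.
- **Schedule for Assessments**: "All participants will be requested to fill the self-report measures at 4 weeks" and at the later visits. Table 2 lists both scales at every self-report visit, with no condition on diagnosis.
- **Clinical Outcomes**: "The secondary clinical outcomes are PAS, LSAS, EQ" and a long list of further scales.
- **Primary Outcomes**, item (4), is the "mean and standard deviation of the below clinical measures at 8 weeks and 5, 8, and 12 months". These two scales are among the measures that follow.
- **Statistical Analysis**: "For primary and secondary clinical outcome analyses, we will analyze mean changes from baseline". The full analysis set is every randomised patient who received at least one treatment procedure. The listed effects are treatment, visit and their interaction.
- **Subgroup Analysis** covers delivery mode only.
- **Randomization** is "stratified by diagnosis (ie, panic disorder/agoraphobia and social anxiety disorder", and also by baseline STAI. No described analysis uses the diagnosis stratum.

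**The concern.** The PAS is applied to patients outside the population that the article itself names for it, and the LSAS to patients who may not have social anxiety disorder. Two consequences follow if the text is carried out as it stands.

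First, the mean and SD of each scale describe a mixture. They move with the share of each diagnosis that happens to be recruited and with the gap between the diagnoses' mean scores. In a feasibility trial these summaries are a stated primary output, and the sample size is justified by the evaluation of an SD.

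Second, the arm difference averages patients for whom the scale is on target with patients for whom it may not be. If the latter respond less on the scale, the difference shrinks.

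**Working it through.** **The plan's own figure.** The Sample Size section gives 50 patients, 2 × 25, from a recommended range of 24 to 50. The arithmetic is consistent. No effect size, SD or power is stated, so there is nothing further to reproduce.

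**Inputs not in the article (assumptions).** Call a patient on target for a scale if he or she has the matching disorder.
- p: share on target, 0.3 to 0.7
- q: off-target effect as a fraction of the on-target effect
- r: off-target SD divided by on-target SD, 0.3 to 1.0
- g: gap between the two groups' means in on-target SDs, 0 to 2

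**1. Pooled SD.** Pooled SD / on-target SD = √[p + (1−p)r² + p(1−p)g²].
- Smallest: p = 0.3, r = 0.3, g = 0: √(0.3 + 0.7 × 0.09) = √0.363 = 0.60.
- Largest: p = 0.5, r = 1, g = 2: √(0.5 + 0.5 + 0.25 × 4) = √2 = 1.41.

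Take a disorder-specific trial planned for a difference of 0.5 on-target SD (two-sided 5%, 80% power). It needs 63 per arm with the on-target SD. With the pooled SD in its place it would be planned at 23 per arm (factor 0.363) or 126 (factor 2). The error can go in either direction.

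**2. Dilution.** Pooled effect / on-target effect = p + (1−p)q.

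| p | q = 0 | q = 0.5 | q = 1 |
|---|---|---|---|
| 0.3 | 0.30 | 0.65 | 1 |
| 0.5 | 0.50 | 0.75 | 1 |
| 0.7 | 0.70 | 0.85 | 1 |

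**3. Does restriction gain power?** With g = 0, the ratio of expected z (restricted set over full set) is √{p[p + (1−p)r²]} / [p + (1−p)q]; the total N cancels. At p = 0.5:

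| r | q = 0 | Ratio is 1 at | q = 0.5 |
|---|---|---|---|
| 0.5 | 0.559/0.5 = 1.12 | q = 0.12 | 0.559/0.75 = 0.75 |
| 1.0 | 0.707/0.5 = 1.41 | q = 0.41 | 0.707/0.75 = 0.94 |

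If off-target patients hardly vary at all (r = 0, q = 0), the ratio is 0.5/0.5 = 1.00 and there is no gain. For p = 0.5, N = 50, q = 0 and an on-target effect of 0.5 SD, power is 24% restricted against 9% to 22% pooled over the r and g values above. It is low either way.

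**4. Price in precision.** The 95% confidence limits for an SD pooled over arms (chi-square, N − 2 df), as multiples of the estimate:

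| N | Limits |
|---|---|
| 50 | 0.83 to 1.25 |
| 25 | 0.78 to 1.40 |
| 15 | 0.73 to 1.61 |

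**The case against.** The other side has several good points.

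- **The analysis plan is not shown.** One general sentence covers all clinical outcomes, and scale-specific populations could be set elsewhere. However, the article does fix the analysis set, the model terms and the only subgroup analysis, and it says that all comparisons are planned. Diagnosis-specific results added later would sit badly with that statement.
- **Only the PAS is tied to a diagnosis.** The LSAS description limits the scale to no disorder. PAS subscales such as anticipatory anxiety and disability could move in social anxiety, and comorbid patients may be on target for both scales. A reader might infer that both effects will shrink by about half. The article gives neither the diagnosis shares nor any off-target effect, so it does not support that.
- **Restriction is not free.** A reader might infer a 12% to 41% gain in expected z. That needs an off-target effect of zero, and the sign reverses once q passes 0.12 (r = 0.5) or 0.41 (r = 1). With the 43 patients reported as enrolled and no comorbidity, one of the two sets has at most 21, below the 24 to 50 that the article cites.
- **The sets may not match the strata.** Randomization names two diagnosis levels without saying where comorbid patients go. The comparison within a baseline diagnosis is still between randomised arms, but its balance is not fully secured by stratification.
- **Pooled SDs have a use.** A reader might infer that no disorder-specific trial could use these data. That goes too far: diagnosis is recorded by SCID, so SDs by diagnosis can be derived. The article does not say that the definitive trial will be disorder-specific, and for the same mixed population the pooled SD is the relevant one.

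These points limit the size of the problem. They do not alter that the described summaries of the two scales mix on-target and off-target patients.

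**Conclusion.** The point holds and is minor. As described, the PAS and LSAS results will depend on the recruitment mix, and the diagnosis stratum goes unused in the analysis. Under the assumed ranges, the pooled SD is 0.60 to 1.41 times the disorder-specific one. Dilution of the arm difference is conditional on a smaller off-target response, and its size cannot be derived from the article. The case for diagnosis-specific reporting rests on interpretable means and SDs, not on power. Both scales are secondary in a trial that calls itself exploratory, and the STAI is not specific to one disorder.

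**What to change.** Prespecify in Statistical Analysis that:

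- PAS means, SDs and arm differences are reported in participants with a baseline SCID diagnosis of panic disorder or agoraphobia;
- LSAS means, SDs and arm differences are reported in participants with a baseline SCID diagnosis of social anxiety disorder, with comorbid patients counted in both sets;
- the number in each set and a confidence interval for each SD are given;
- full-analysis-set results for both scales stay alongside, for use in planning a definitive trial in the same mixed population.

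A diagnosis term added to the pooled model would not be enough, since the arm difference would still be an average over both groups.

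The change takes a sentence or two and needs no new data, because the SCID diagnosis is already collected. Its cost is a smaller n and wider SD intervals on two secondary scales.
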